## 2. Research plan

### 2.1. Current state of research in the field

In recent decades, the proportion of women medical students has increased worldwide and has even outmatched their representation in the general population. This contrasts with the underrepresentation of women in leadership and academic positions. According to the Swiss Medical Association (FMH), only 12% of senior doctors heading a medical service in 2018 were women. In 2012, only 18% of full or associate professors in Swiss Universities were women. Local demographic statistics at the Faculty of Medicine of the University of Geneva (UNIGE) are in line with worldwide findings on the underrepresentation of women among professors. While for the last two decades more than 60% of students have been women, the proportion of women professors at UNIGE is still dramatically low, at 6% in 2000, 16% in 2010, and 21% in 2015. Various reasons might explain this gender imbalance, the first being that women face greater difficulties in managing an academic career, partnership and family. Women more frequently put family duties before their careers. Another reason (and not the least) is the existence of gender bias at different stages of medical studies and academic training. During medical school, gender and generation are both important influences on career and specialty choices. Thereafter, women face more gender discrimination and have more difficulties than men in finding a mentor to help manage their career and facilitate their advancement and productivity. Women scientists are also less likely to get funded for their research due to a less favourable assessment of grants written by women principal investigators and not due to differences in the quality of proposals led by men and women. In another experiment, gender bias against women was demonstrated in the assessment of student application materials for a laboratory manager position when they were randomly assigned either a male or a female name. Finally, in the area of medical publication, a gender imbalance is striking: only 33% and 18% of first and last authors, respectively, are women. Though the representation of women first authors increased significantly between 2000 and 2015, it still remains well below 50% and thus does not reflect the current "feminisation" of the medical profession. During the early period of pandemic, we observed increased gender disparities in attainment of co-authorship positions on submitted research related to covid-19 which narrowed in the second year of the pandemic. Because academic promotion and awarding of research grants are heavily influenced by the publication records of candidates, and competition for prominent authorship positions (first, last, corresponding) is high, there is an urgent need to take into account the inequalities in terms of scientific production to the detriment of women. This helps explain the gender gap against women regarding their scientific productivity and thus their difficulties to be promoted. Beyond the medical sciences, the influence of gender on peer review outcomes has also been assessed and has revealed contrasting

results. We recently reported a double gender and geographical bias in the invitation and participation to the peer review process. Women are less invited to peer review (39% women among invited peer reviewers) compounded by fewer women agreeing to peer review invitations (31% women agreed vs. 38% of men). Reviewers with African, Asian and South American affiliations and those from low- and middle-income countries are underrepresented, even when they were more likely to agree to review.

With regards to the division of labour in research, similar to the findings from other studies, our analysis of published article contribution statements found there are significant differences between men and women authors: men are more frequently assigned tasks considered more prestigious, such as conception and study design, fundraising, data analysis, and paper writing, while women are assigned more operational tasks such as data collection, logistics and administrative support. These differences could explain why women are less likely to be last author compared to men as reported elsewhere. Women were more frequently second authors and less likely next-to-last authors compared to men. Some characteristics of submitted manuscripts, such as study design, analytical methods, disclosure of funding source and country where the research took place were also independently associated with acceptance for publication. It is also possible that within research collaborations, women are frequently offered first or last authorship on secondary less important and lower-quality papers. If this were the case, we would expect to find that women are more frequently authoring papers of lower quality or that women are more frequently first authors of papers presenting results from ancillary or *post-hoc* studies. This would also explain why women have fewer publications and citation rates compared to men, and thus have lower h-indices.

While we have identified a gender gap generally in the research process, to our knowledge, no studies have yet explored specifically the existence of gender bias at the final stage of the publishing process: when the editor of a medical journal decides to accept or decline a submitted research manuscript. The existence of geographical and income-country bias has not been further investigated in the acceptance for publication.

## 2.2. Current state of your own research

In 2015, we assessed professors' h-indices in a local survey of UNIGE's Faculty of Medicine and showed that they were significantly lower among women (mean  $22.4 \pm 15.1$  versus  $32.0 \pm 10.3$ ,  $p=0.001$ ), whether in clinical medicine or basic sciences. This discrepancy persisted throughout a period during which several initiatives for promoting women in academia had been launched. Among clinical-medicine professors, women published significantly fewer papers than their male counterparts at the time of the assessment (mean 92 papers  $\pm 59$  versus  $163 \pm 107$ ,  $p<0.001$ ). The results of this survey were not published; the manuscript was rejected from seven peer-reviewed journals. The main criticism was a (perceived) lack of generalizability of its findings (personal communication). The study dataset is, however, available in a public repository (<https://easy.dans.knaw.nl/ui/datasets/id/easy-dataset:76777>). Though never published, its results triggered the implementation of studies aiming to better understand the drivers of gender inequity in scientific productivity and thus to promote women more effectively in academia. Currently, we do not fully understand such differences; one possibility is that men and women researchers essentially contribute equally, but are not rewarded equitably by grants, author roles or tenured positions. Alternatively, the roles of men and women researchers may be different

due to different trajectories during their training, in which case, unequal rewards would be merely a consequence of these different skills and contributions.

The research-hypothesis framework is presented in Figure 1 below. We assessed this research question in a cross-sectional study of original articles published 15 years apart in a single, widely cited US-based medical journal that provides a constant and standard format for reporting author contributions, in contrast to other journals. Our results highlight that research roles are not distributed equally between women and men researchers and that these differences have remained unchanged over a 15-year period. This may be due to justifiable reasons as explained above. However, it is also possible that the academic research milieu perpetuates sexist attitudes and unequal treatment of researchers based solely on their gender. Before we launched ATHENA, we conducted an ancillary study where we explored women's visibility at three important authorship positions (first, last, and corresponding) during the Covid-19 pandemic among 11 biomedical journals from the BMJ Publishing Group. We showed that gender disparities were accentuated for Covid-19 related manuscripts early in the pandemic. These gender disparities in submitted manuscripts narrowed in the most recent pandemic period (Feb-May 2021) compared with the early pandemic (Jan-May 2020). In a second ancillary study, we confirmed the existence of gender and geographical biases during the peer reviewing process which widened during the pandemic.

While we have confirmed others' results that a gender gap may exist at various points during the research process, exploration of gender bias at the point of manuscript evaluation by editors of academic journals is warranted. In a preliminary analysis of all original articles submitted between July and December 2017 to the journal *Clinical Microbiology and Infection*, we found—paradoxically—that women first authors, though fewer in number, had significantly higher acceptance for publication than their male counterparts (45% versus 27%,  $p=0.003$ ); the editor's gender had no effect on rates of acceptance. This unexpected result obtained in a single journal specializing in infectious diseases and clinical microbiology from original articles submitted over a six-month period is unlikely to be generalizable. Furthermore, gender bias should be assessed in multivariate analyses, independently of other study attributes known to be associated with chances of publication. It has, however, heightened our motivation to test the research hypothesis on a larger sample of journals from various medical domains.

Access to such data is difficult to obtain. The BMJ Publishing Group has agreed to participate and we have received the data of all submissions between January 1, 2012 and May 31, 2021 from 11 of its journals. Four additional journals have also agreed to participate in the ATHENA project (*Clinical Microbiology & Infection*, *Infection Control and Hospital Epidemiology*, *British Journal of Anaesthesiology*, *Journal of Antimicrobial Chemotherapy*); three of these have already sent 120 pdfs (60 manuscripts accepted for publication and 60 manuscripts rejected after review) as a pilot study for assessing feasibility. The *Lancet Infectious Diseases* agreed to participate but would not provide pdfs of the manuscripts; they sent all the data initially defined in the protocol from 60 manuscripts accepted for publication and 60 manuscripts rejected after review. All journals that we contacted are presented in Appendix 2 and those who agreed to participate have sent letters of support (Appendices 3 to 6). So we have carefully and successfully woven together a network of journals representing a range of specialties and impact factors whose editors are willing to explore with us the possibility of gender and other biases in their editorial decision-making processes in order to define the problem, if any, and thereafter to identify strategies to solve it.

**Figure 1.** Framework of possible mechanisms explaining gender bias in the authorship of scientific publications and academic promotion (adapted from reference).

[figure not shown]

## 2.3. Detailed research plan

### 2.3.1. Study rationale

As stated before, while a gender gap is clearly present in the conduct and publication of medical research, no one has yet specifically explored whether that gap could at least partially be due to a bias in journal editors' decisions to accept or decline a submitted manuscript. We propose here to assess the existence of gender bias throughout the editorial decision-making of several medical journals.

### 2.3.2. Aim and hypothesis

We postulate that acceptance rates for publication should differ by a factor 0.85 between women and men first authors among leading medical journals to confirm a gender bias. We aim to identify the influence of first-author gender on acceptance rates among original research articles sent for peer review by leading medical journals over an eight-year period.

### 2.3.3. Objectives

Our **primary objective** is to evaluate the influence of first-author gender on acceptance rates of original articles submitted to leading medical journals that were sent for peer review.

Our **secondary objectives** are: 1) to study the influence of corresponding-author gender and last-author gender on acceptance for publication; 2) to test whether the editor's or associate editor's (see glossary) gender modifies the influence of author gender on acceptance for publication; 3) to determine whether the influence of author gender on acceptance for publication varies over an eight-year period; 4) to determine the proportion of women first authors at each stage of the editorial decision-making process; 5) to possibly explore whether the reasons for manuscript rejection differ between women and men first, last and corresponding authors.

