### **1.4. Expected results and their impact**

If we observe that the likelihood of acceptance is at least 0.85 (odds ratio) for women compared to men first authors, it will contribute to our understanding of why women have lower publication rates and thus make slower

progress in academia. Thereafter interventions, such as editor anonymising regarding the author's name, could be assessed. Other methods are already implemented in some journals, such as fully open peer review journals where authors and reviewers are named, and this might impact on results as well. If we do not find gender bias in editors' and reviewers' decision-making, we will be able to conclude that the imbalance in gender inequality is more likely due to discrimination upstream to the editorial decision-making step. This would justify the continuation and expansion of institutional initiatives for mentorship and promotion of women's careers in sciences and unconscious bias training for editors as well as the importance of journals collecting and reporting on the gender of authors and peer reviewers.

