##### **2.3.5.2. Case-control study**

The study population will be original research articles and systematic reviews submitted to participating journals that were externally peer reviewed and which focus on clinical and/or translational research. Original articles presenting results of non-human or basic-science research (animals, *in vitro*) will be excluded, as will non-research articles (clinical review articles, editorials, commentaries, protocols and letters). All articles where we are unable to identify the gender of the first author will be excluded.

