### 2.3.7. Outcome measures and data collection

#### 2.3.7.1. Outcomes

In the case-control study, cases (primary outcome) will be **articles accepted for publication after peer review** and controls will be **articles rejected for publication after peer review**.

In the retrospective cohort study, **the acceptance rate of all submitted articles** by gender of first, last and corresponding author (secondary outcomes), will be determined. All original research articles and systematic reviews will be included. Additionally, we will record the rates of “reject without peer review”, revision requests, and later rejection throughout the manuscript’s cycle.

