## 2.5. Relevance and impact

### 2.5.1. Scientific relevance

Before it can reach publication, an original article is left in the hands of individuals in the editorial team who could, as in society, apply their own rules and possibly gender discrimination, whether consciously or not. All submitted manuscripts go through a preliminary editorial screening during which assessments are made as to whether the topic is within the journal's scope, author instructions were respected, and general quality standards are met; it is then sent out for peer review; once the required number of reviews is received, the editor(s) consider the experts' opinions and make an initial decision to accept, reject or request revision, or take it to a committee and/or statistical reviewer for further assessment. Revised papers are re-evaluated by the original handling editor, who either makes a decision (or refers it back to a committee that may include a statistical advisor) or sends the manuscript for further peer review prior to making a decision. Editors may request multiple manuscript revisions. This editorial decision-making process may vary in the assessment criteria used, depending on the journals; the final decision could be left to a single individual (the handling editor) or to a group of persons (Figure 2). The BMJ, one of the largest participating journals, includes patient and public reviewers in the review process (Figure 3).

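### The primary odds ratio covers only papers already sent for review, so a null result cannot on its own place the gender imbalance upstream of editorial decision-making

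*Protocol*

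**What the plan says.** Section 2.3.1 sets a wide scope: "We propose here to assess the existence of gender bias throughout the editorial decision-making of several medical journals". The primary objective in Section 2.3.3 is narrower: "to evaluate the influence of first-author gender on acceptance rates of original articles submitted to leading medical journals that were sent for peer review". Section 2.3.5.2 draws the case-control sample from articles "submitted to participating journals that were externally peer reviewed and which focus on clinical and/or translational research". Section 2.3.7.1 defines cases as "articles accepted for publication after peer review" and controls as "articles rejected for publication after peer review".

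Section 2.5.1 describes the step before review: "All submitted manuscripts go through a preliminary editorial screening during which assessments are made". That screen covers scope, author instructions and general quality. The covariates in Section 2.3.7.2 and Appendix 7 are attributes of the study and its authors, editors and reviewers; none measures manuscript quality directly.

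Section 1.4 states what follows if no bias is found in the decisions of editors and reviewers: "we will be able to conclude that the imbalance in gender inequality is more likely due to discrimination upstream to the editorial decision-making step". Its only numerical criterion is an OR of 0.85, which Section 2.3.9.1 ties to the case-control study. Section 2.5.2 likewise foresees moving attention and resources to earlier points in the pipeline.

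The desk stage is not ignored. Section 1.2 (aim 4) covers decision points from submission onwards. Section 2.3.3 (secondary objective 4) asks for the proportion of women first authors at each stage. Section 2.3.7.1 makes acceptance among all submissions a secondary outcome. Section 2.3.9.2 compares the proportion of women at each stage, and for rejection at any stage against acceptance, by Chi-2 tests.

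**The concern.** There are two separate problems.

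1. **Coverage.** An OR among reviewed papers cannot detect a disadvantage that acts at the desk. If the upstream conclusion were drawn from a null primary OR, an editorial disadvantage at the desk would be attributed to causes outside the journal.
2. **Selection.** The sample is conditioned on a decision that belongs to the process under study. If women's papers face a higher bar at the desk, those that reach review are better on average. Where that extra quality also helps at the final decision and the covariates do not capture it, the after-review OR rises.

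At stake is what the study may claim from a null result, which the protocol itself presents as guidance on where to direct later effort.

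**Working it through.** **The plan's own effect size.** With 40% women among cases and 44% among controls (2.3.9.1), OR = (0.40/0.60)/(0.44/0.56) = 0.667/0.786 = 0.85. This reproduces. It is an after-review OR, because both groups consist of reviewed papers.

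**Coverage, without any quality mechanism.** Assumed inputs, since the protocol gives no desk pass rate: 40% of men's papers pass the desk; 35% of reviewed papers are accepted for both genders; desk OR for women 0.70.
- Women's desk odds: (0.40/0.60) × 0.70 = 0.467, so 31.8% pass.
- After-review OR: 35% against 35% = 1.00.
- Accepted from submission: men 0.40 × 0.35 = 0.140; women 0.318 × 0.35 = 0.111.
- Submission-to-acceptance OR: (0.1114/0.8886)/(0.140/0.860) = 0.77.

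With desk OR 0.85 the same steps give 36.2% passing, 0.1266 accepted and an OR of 0.89. The primary OR is 1.00 in both cases.

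**Selection.** Unmeasured quality q is N(0,1) in both genders.
- Desk: logit P(sent) = a_g + b_d·q. The men's intercept gives their pass rate; the women's intercept gives the chosen marginal desk OR.
- Final decision: logit P(accept | sent) = c + b_r·q + ln(R)·woman. The intercept c gives 35% acceptance of men's reviewed papers. R is the true gender effect after review.
- A_g is P(accept | sent) averaged over q among reviewed papers. After-review OR = odds(A_w)/odds(A_m). Submission-to-acceptance OR = odds(P_w·A_w)/odds(P_m·A_m), where P_g is the desk pass rate.

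Assumed ranges: men's pass rate 30-50%, b_d 1-2, b_r 0.5-1.5. Results by numerical integration:

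| Desk OR | R | After-review OR | Submission-to-acceptance OR |
|---|---|---|---|
| 0.85 | 1 | 1.016-1.065 | 0.889-0.945 |
| 0.70 | 1 | 1.034-1.149 | 0.767-0.875 |
| 1.18 | 1 | 0.938-0.984 | 1.053-1.122 |
| 1.00 | 0.85 | 0.854-0.885 | 0.882-0.914 |
| 0.85 | 0.85 | 0.869-0.936 | 0.793-0.855 |
| 0.70 | 0.85 | 0.885-1.009 | 0.686-0.795 |

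Reading the table:
- The fourth row has no gendered screening, yet 0.85 already appears as 0.854-0.885. That is non-collapsibility of the OR over unmeasured quality, not selection.
- Dividing the last two rows by the fourth at the same inputs leaves a selection factor of 1.016-1.065 and 1.034-1.149, the same as in the first two rows.
- Setting b_d or b_r to zero gives a factor of exactly 1.
- Screening that favours women (third row) moves the OR down.

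A second parameterisation (40% desk pass, 40% acceptance after review, desk OR conditional on quality, slopes 1 to 2) gives factors of 1.025-1.046 at desk OR 0.85 and 1.055-1.105 at desk OR 0.70. Direction and size agree.

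**The case against.** The case for the plan is substantial.

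- **The primary objective is already conditional on review.** This stands; Section 2.3.3 needs no change.
- **Desk-stage and all-submission comparisons are planned.** This also stands, and it would be wrong to say that the plan overlooks the desk. But Section 2.3.9.2 specifies Chi-2 tests for them, with no adjustment for journal. Across 23 journals, both the desk rejection rate and the share of women first authors may differ, so a pooled comparison can mix journal differences with gender differences. The same section uses journal as a random effect in the case-control model for this kind of reason.
- **Section 1.4 speaks of decisions by editors and reviewers in general, and says only that an upstream cause is more likely.** Fair. It can be read as resting on all stages, but it does not say so, and its one numerical criterion belongs to the reviewed-only sample.

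A reader might infer that gendered screening necessarily raises the primary OR and so hides the bias. The documents do not support that. They give no desk rates by gender, and the shift needs both stricter screening of women and a residual quality link at both stages. Adjustment for study attributes, which the model above leaves out, may remove part of it.

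A reader might also take the preliminary result in Section 2.2 (45% of women's papers accepted against 27% of men's) as a sign of this mechanism. It concerns all submitted articles at one journal, so it is not a post-screening figure.

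**Conclusion.** The point holds as a limit on what may be concluded. A null primary OR speaks only to the stage after review and cannot by itself support the upstream conclusion in Section 1.4. This part needs no modelling assumption: it follows from the sample definition and from the fact that desk rejection is an editorial decision.

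The selection shift is a secondary and conditional concern: about 2-7% upward at desk OR 0.85 and 3-15% at desk OR 0.70, under assumed pass rates, acceptance rate and quality slopes. At a desk bias equal to the study's target effect it is modest. Bringing a true after-review 0.85 to about 1 took a desk OR of 0.70 with the steepest slopes examined. The stronger reading, that the primary design conceals the bias the study seeks, is not established.

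**What to change.** 1. Leave the primary analysis and the objective in Section 2.3.3 as they are.
2. In Section 2.3.9.2, report two cohort estimates by first-author gender, each with a confidence interval: the desk-stage OR and the submission-to-acceptance OR. Use the mixed-effects logistic model with journal as random effect, in place of or alongside the pooled Chi-2 tests. Any covariates should be ones known at submission, because the reviewer and revision counts in Appendix 8 do not exist for desk-rejected papers.
3. In Sections 1.4 and 2.5.2, limit the conclusion from a null primary OR to the post-review stage. Allow the upstream conclusion only if the confidence intervals of both cohort ORs also exclude a relevant disadvantage, for example the protocol's own 0.85.

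The cost is a little more analysis and a narrower conclusion. Appendix 8 already holds first-author gender, journal identifier and final decision, including immediate rejection, so no new data are needed.
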